#### Health professionals who referred carers to the CHWS.

Any health professional providing two or more referrals to the CHWS (e.g., general practitioner, allied health professionals, geriatrics services and specialist clinics) will be invited to participate in the study evaluation through a semi-structured interview. Invitations to participate in the interviews will be sent through the CHWS manager to referrers, who will be asked to contact a member of the research team if interested in being involved. Referrers will be asked to provide written informed consent to take part in the interview.

### Procedure: Service screening and assessment tools

#### Older carers (n=137).

An episode of care for carers attending the CHWS is up to 6 months in duration, although this may vary depending on individual carer needs. Fig 2 shows the referral, assessment and intervention flow for carers referred to the CHWS. Referrals will be received by the CHWS manager or administrative support person, using a standard intake referral form (Access form) either through the Peninsula Health Access Manager (the usual process for referral intake/processing at Peninsula Health), or direct from the referrer to the CHWS administrative person. The carer will then be contacted by the CHWS manager or administrative support person to undergo orientation to the CHWS and associated study, involving six steps:

**Fig 2 pone.0326363.g002:**
[figure not shown]
Referral, assessment and intervention processes for the Carers Health and Wellbeing Service (CHWS).

a)Description of CHWS purpose and processes (if not provided by the referrer to the carer);b)Screening demographic questions and questions to ensure the carer meets the inclusion criteria for participating in the CHWS;c)Description of the option for participation in the research study and their participant data being used as part of the CHWS evaluation (and the need for signed informed consent for this to occur) (Note: consent to participate in the research is not a prerequisite to use the CHWS services, so those not providing consent for the research will still work through all the CHWS processes, but the research team will not have access to their data);d)Introduction to the CSNAT, and request for the carer to review and reflect on the CSNAT questions in preparation for the initial CHWS assessment (which will be the same process whether it is conducted face-to-face or online);e)Carers’ initial perception of the main area/s they are seeking assistance, information, advice or interventions to assist them to maintain or improve their own health and wellbeing (to guide decision-making by CHWS staff regarding the most appropriate team member (discipline) to conduct the initial assessment – this will be accommodated as best as possible based on information provided and availability of the relevant staff member). Adjustments may be made in terms of the CHWS staff member to undertake the initial assessment to minimise delays in commencement with the services if required; andf)Preferred mode of Service participation (in-person or online), and preferred mode for receiving information from the Service (email, phone, post).

The carer’s first appointment will be scheduled where possible with the CHWS staff member whose professional expertise best aligns with the primary needs identified by the carer during screening. This staff member will be designated the carer’s key contact person, who will assume overall primary contact and oversight of the carer’s CHWS management. The first appointment will have a focus on: completing all core assessments (Table 1); identifying prioritised carer needs (up to three top prioritised needs, based on the carer views in the context of the CSNAT and any other needs); and shared decision-making regarding initial area/s to address and intervention/s (what matters most).

**Table 1 pone.0326363.t001:** Core assessments (used for all CHWS clients) and bespoke assessments (used depending upon prioritised needs being addressed for individual clients).

Measure^*^	Description
**CORE ASSESSMENTS**	
Carer Support Needs Assessment Tool (CSNAT) [31,35]^*^.	The CSNAT is a 14-item tool (seven domains of support enabling the carer to care, and seven domains of support relating to their own wellbeing), used to obtain information on and prioritise carer’s support needs. It can be used as both a research tool and as part of a practice intervention (staff using the CSNAT will undergo required training). *The CSNAT will not be used as an outcome measure, as recommended by the tool developers.*
Preparedness for Caregiving Scale (PCS) [34]^*^.	**Primary outcome measure.** The PCS includes eight items evaluating how prepared carers consider themselves to be for different aspects of caregiving. Each item is rated on a five-point scale (0 = not at all prepared; 4 = very well prepared). Higher scores indicate better preparedness for caregiving. Components of the PCS and overall PCS score have been shown to be responsive to change in a nurse-led intervention for family carers of older people being discharged from hospital [36].
EuroQoL Five Dimension Five Level scale (EQ-5D-5L) [37]^*^.	The EQ-5D-5L is a widely utilised measure of quality of life that is also used in health economic evaluations. For this study, the five domains of the EQ-5D-5L (mobility, self-care, usual activities, pain/discomfort and anxiety/depression) will be assessed, each on five levels (no problems, slight problems, moderate problems, severe problems and extreme problems).
Family Appraisal of Caregiving Questionnaire (FACQ) [38]^*^.	The FACQ has 26 items, rated on a 5-point scale ranging from 1 (strongly disagree) to 5 (strongly agree). The 26 items are grouped into four subscales, including: caregiver strain, positive caregiving appraisals, caregiver distress, and family wellbeing.
Health economics survey to capture care related data and health care utilisation data including emergency department and hospital admissions over the past 6 months^*^	This survey will ask average weekly hours of care provided by the carer, by other people who are not paid, and by other people who are paid; as well as capture the “preferred” and “actual” weekly hours the carer spends on their top three leisure activities (where the carer role contributes to the gap between “preferred” and “actual” hours of participation). It will also include self-report health care utilisation information. This information will be used in the cost utility analysis.
**BESPOKE ASSESSMENTS** ^**^	
**Psychological health and wellbeing**	
Depression, Anxiety and Stress: The 21-item (short form) Depression, Anxiety and Stress Scale (DASS-21) [39]^*^.	This self-report scale measures the negative emotional states of depression, anxiety and stress, and has been shown to have sound psychometric properties with older people [44]. Given the tool is designed to measure a number of constructs, this reduces the need for multiple scales across these constructs, thereby reducing potential burden for participants.
Loneliness: The De Jong Gierveld 6-item Loneliness Scale [40]^*^.	The six items are scored yes, more or less, or no and focus on emotional and social loneliness.
Social participation: the abbreviated Lubben Social Network Scale (LSNS-6) [41]^*^.	The LSNS-6 consists of three items in each of a Family domain and a Friendship domain. Each item is rated on a 0–5 rating scale.
Psychosocial assessment ^*^	An in-depth discussion to understand the experiences of the caregiver both as an individual and within the context of their family and community. This type of assessment is used to identify potential strengths and resources available to caregivers, as well as possible challenges within their social context that could be addressed to improve health and wellbeing.
**Physical performance**	
Level of physical activity: The Physical Activity Scale for the Elderly (PASE) [42]^*^.	The PACE includes evaluation of leisure, household and occupational activity, that can be combined (utilising frequency, duration and intensity level of the physical activity) to derive an indicator of the level of light, moderate and vigorous physical activity.
Lower limb muscle strength: using the Five Times Sit-to-Stand Test [43].	Participants will be asked to sit on a chair (43 cm high), stand up (with arms crossed over their chest if possible) and sit back down five times as quickly as possible. The time taken to perform five complete sit-to-stands will be measured (seconds). If unable to stand up with arms crossed over their chest, participants will be asked to perform the task allowing pushing up with their arms (with use of arms documented). Performance will be timed in the same way if arms are used.
Dynamic balance: Four Square Step Test – a dynamic rapid weight shifting and stepping in multiple directions task [44].	Four walking canes (or similar) are set up in a + shape on the floor; the participant stands in the left forward quadrant facing forward. When instructed to start, they step as quickly as possible for both feet to be positioned in the right forward quadrant, then backwards for both feet to be in the right backwards quadrant, then to the left to be in the left backwards quadrant, then forwards to the starting quadrant; and then reverses the stepping procedure. Timing of the task stops when the person returns to starting position again (i.e., has stepped in 4 quadrants clockwise and four quadrants anticlockwise).
Balance and mobility: The de Morton Mobility Index (DEMMI) [45].	The DEMMI is a 15-item test of balance and mobility. Items are hierarchically ordered, so if a person is unable to perform lower-ordered items, they will not be able to do higher-ordered items. Scores will be converted to a RASCH analysed score for analyses [41].
**Function**	
Activities of Daily Living (ADL): the Barthel Index [46]^*^.	The Barthel Index is widely used to assess functional independence. It uses an ordinal scale across 10 domains of ADL or mobility activities.
Instrumental ADL (IADL): the Lawton and Brody Instrumental Activities of Daily Living Scale [47]^*^.	This eight-item tool assesses activities such as shopping, the ability to handle finances, and handling own medicines. Each item has between three to five response options, each scored as 0 or 1.
Functional competence: the 12-item Occupational Self-Assessment-Short Form (OSA-SF) [48]^*^.	The OSA-SF enables self-reporting of perceived competence across areas of performance/participation and the level of importance of the activity for the individual.
Sleep quality/disturbance will be assessed through the Insomnia Severity Index (ISI) [49]^*^ and the Epworth Sleepiness Scale (ESS), respectively [50]^*^.	The ISI is a 7-item screen (with a 5-point Likert scale) to assess the nature, severity and impact of insomnia. The ESS is an 8-item self-administered questionnaire where respondents rate, between 0–3 their chance (from never to high chance) of dozing off during 8 activities. Both tools are brief and have strong psychometrics.
Fatigue: The 13-item Functional Assessment of Chronic Illness Therapy (FACIT) Fatigue Scale [51]^*^.	The FACIT Fatigue Scale is measured on a 4-point Likert scale and is specifically designed to assess fatigue in older adults.
**Other measures**	
Cognition	The Montreal Cognitive Assessment (MoCA) (ST) [52]; Rowland Universal Dementia Assessment Scale (RUDAS) [53]; Trail Making Test (TMT) (A) [54].
Nutrition^*^	The Mini Nutritional Assessment-Short Form (MNA-SF) (ST) [55].
Pain^*^	Verbal Descriptor Scale (VDS) (ST) [56].

* Within each assessment domain, at least one of the assessment tools will be able to be undertaken remotely, or is a questionnaire, to enable some outcomes to be evaluated for carers who are only able to attend the CHWS remotely. These tools are denoted with an asterisk.

** Bespoke assessment tools will be selected upon need, as determined by the CHWS staff member, based on prioritised area/s of need by the carer.

Assessment tools for carers, where applicable, will be utilised both as outcome measures and to inform possible interventions (e.g., data from the physical performance assessments may guide the type of exercises to include in a home exercise or physical activity program) (Table 1). Assessment tools are listed in Table 1 as (1) Core assessment tools, to be administered to all carers on initial assessment; and (2) Bespoke assessment tools, listed under the domains of psychological health and wellbeing, physical performance, function, and other assessments. One or more bespoke assessment tools will be utilised depending on the domains or areas of need prioritised by carers to be addressed through the CHWS intervention. The primary effectiveness outcome measure will be the Preparedness for Caregiving Scale [34]. All assessments may be performed by any of the CHWS staff (who will all be trained in their use) although it is anticipated in most cases the physical performance assessment will be undertaken by the physiotherapist, functional assessments by the occupational therapist, and psychological health and wellbeing assessments by the psychologist or social worker. For each domain, at least one of the assessment tools will be able to be undertaken remotely, or be a questionnaire, to enable some outcomes to be evaluated for carers who are only able to attend the CHWS remotely. Although the CSNAT data will be recorded to document carer-prioritised needs at baseline, at the 6 months assessment it will only be used to ask carers if the initially prioritised needs have been (1) fully addressed; (2) partially addressed/ still being worked on; or (3) unchanged (still remains a major prioritised need).

Assessments will occur at initial intake assessment, and 6 months later, as the Service will operate typically with a 6 month episode of care. However, for carers who feel their needs have been fully met earlier than 6 months, the final assessment will be brought forward. For carers who may still have active issue/s being worked on with staff, a 6 month assessment will be completed (to be used in main data analysis), and a final assessment undertaken at a later time point when the episode of care is completed.

Depending on the identified carer prioritised needs and shared decision-making, the CHWS staff member (or another staff member if more relevant) will undertake one or more additional bespoke assessments related to the area/s of need identified. For example, if the areas of need related to depression and poor sleep, additional assessments could include the 21-item (short form) Depression, Anxiety and Stress Scale (DASS-21) [39,57], the Insomnia Severity Index (ISI) [49], and the Epworth Sleepiness Scale (ESS) [50]. Table 1 lists the main bespoke assessment tools that will be utilised depending upon the prioritised needs of the carer. Additional assessment tools may be selected by the CHWS staff member if a domain of interest is not covered by the bespoke tools listed in Table 1.

As well as the core and bespoke (individualised) assessment tools used for each carer, the Client Satisfaction Questionnaire (8-item, CSQ-8) will be completed by all carers [58]. Additional client satisfaction questions will evaluate carer perspectives of the CHWS referral processes, carer needs prioritisation processes, assessments, interventions, interactions and communications with CHWS staff, modality of interactions with CHWS (face to face or online, or hybrid/ mix), referrals from CHWS and communications with other relevant medical or health professionals, access to relevant information and resources, timeliness of processes and communications, and what they considered worked well and what aspects did not work well. The CSQ-8 and additional service satisfaction questions will be available online (through Qualtrics) or in hard copy. The additional satisfaction questions will be rated using a 7-point Likert scale response, as well as some open-ended questions.

A purposeful sample of approximately 15–25 carers completing the 6 month assessment will also be asked if they are willing to participate in a semi-structured interview (estimated duration 45 minutes). The sample size for interviews will be determined by data saturation. Interviews will be conducted by an experienced qualitative researcher face-to-face or online, dependent upon the preference of the carer, and will be recorded to ensure the accuracy of reporting and analysis. The interviews will explore in more depth the questions in the CHWS satisfaction survey, as well as seek perspectives about recommendations on how the CHWS could be improved. Carers who participate in the interviews will be provided with a $AUD50 gift card as an acknowledgement of their time contribution.

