## Abstract

Older carers (≥50 years) of older people (≥65 years) are an important sub-group of carers performing valuable roles in providing informal care but often do not have the time or give priority to supporting their own health and wellbeing. Current services supporting older carers’ health and wellbeing are fragmented and inadequate. Through previous research and co-design activity by our team, an innovative multidisciplinary Carer Health and Wellbeing Service (CHWS) has been developed. The purpose of this protocol paper is to describe the rationale for the CHWS and the methods proposed to evaluate its effectiveness and implementation outcomes. The CHWS commenced in March 2024 at Peninsula Health, Melbourne, Australia. Older carers of older people can be referred from multiple sources, including self-referral. A pre-post mixed methods study design is being utilised. Initial assessments include the Carer Support Assessment Needs Tool (CSNAT) and carer prioritisation of their needs, which guides further assessment and interventions. Assessments will occur at Service intake and 6 months later. The primary effectiveness outcome is the Preparedness for Caregiving Scale, and primary implementation outcomes are reach and adoption. Interviews of carers, referrers and staff, and a cost-utility analysis will be undertaken. The target sample size is 137 carers undertaking assessment and intervention over the 15 months data collection. Generalised linear regression will be used to compare pre- and post-continuous outcome measures. Qualitative data will be thematically analysed. Results will inform future scaling up of this innovative approach to optimising health and wellbeing of older carers of older people.

**Trial registration number:** Australian New Zealand Clinical Trials Registry (ANZCTR) – ACTRN: 12625000245493.

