#### Subsequent appointments and episode of care.

CHWS staff may schedule face-to-face, phone or online appointments with carers to follow up on aspects of interventions or activities after the first appointment, at a frequency that is mutually agreed upon between the carer and the staff member.

Carer involvement with the CHWS will last an average of 6 months (episode of care), from initial contact to final assessment, **with a standard episode of care being six months duration**, from the time of completion of the initial assessments. The decision regarding discharge timing will be made by the CHWS Primary contact staff member and the carer.

Although it is anticipated that the standard episode of care will be six months, carers with ongoing needs being actively addressed by the CHWS or who have added one or more extra interventions during the 6 month period may opt to continue with the Service beyond the 6 month mark. Those who complete an episode of care with the CHWS can be re-referred if their circumstances change, or new issues arise.

For situations where the person being cared for transitions from home to residential care (for permanent care, not for respite care), or in situations where a care-recipient passes away during the episode of care for the carer, the carer will have the option to continue with CHWS support (with review to determine if needs have changed), or to cease involvement with the CHWS (with re-assessment at this time point if this is acceptable to the carer).

The level of risk for adverse events associated with participating in the CHWS is considered low. If an adverse event occurs, it will be reported to the CHWS Manager, and then to the research team, who will inform the Ethics Committee. The health professional/s involved will provide or organise short term assistance and care as required, including supporting seeking medical support.

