### Data analysis

Extracted data for the CHWS evaluation comparing baseline and 6 month assessment data will be analysed using parametric analyses for continuous, normally distributed data, and non-parametric analyses for categorical or non-normally distributed data. Analyses for comparison of the continuous core and additional domain assessment between initial and 6 month assessments will be performed using generalised linear regression. Analyses will be conducted on an intention-to-treat basis.

Analysis for the cost effectiveness evaluation will involve the costing of items based on actual costs where available, and where these are not available, costs, excluding carer time, will be based on market rates, with carer time based on the minimum wage. All costs will be presented as AUD 2025/26, with costs collected prior to 2025/26 to be inflated by CPI [60]. The EQ-5D-5L raw scores will be converted to a utility index using Australian weights [61], and then into QALYs. The ICER will be calculated using the bootstrap method (5,000 replications) with the results presented on a cost-effectiveness plane and as a probability of cost-effectiveness across a range of willingness to pay thresholds (AUD $0 to $50,000) [62].

For the qualitative study (semi-structured interviews) of carers and referrers, recruitment will continue until data saturation for the carers and the referrers groups. Thematic analyses will be undertaken independently by two members of the research team for each participant group, using Braun and Clarke’s six stages of reflexive thematic analysis [63]. In cases of disagreement between the coders, the two team members will discuss their perspectives to achieve agreement on themes. The thematic analyses will then be presented to a subgroup of the research team and the CHWS staff (n = 6) to review and discuss themes, for finalisation of the thematic analysis for each participant group. A similar approach will be used for analysis of the CHWS staff interviews, although the number of interviews will be small and constrained by the number of current staff, together with interviews with any staff who leave the service. Commonalities and differences in themes between the participant groups will be identified. All quotes to support themes will be de-identified.

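### Carers who finish early have only a brought-forward post assessment, which does not match the 6-month comparison, the 6-month utility change or the 6-month cost recall

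*Protocol article*

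**What the plan says.** All references are to the Protocol article.

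- **Planned times.** The Abstract states: "Assessments will occur at Service intake and 6 months later". The text after Table 1 repeats it: "Assessments will occur at initial intake assessment, and 6 months later, as the Service will operate typically with a 6 month episode of care".
- **Early finishers.** The next sentence makes an exception: "for carers who feel their needs have been fully met earlier than 6 months, the final assessment will be brought forward". No later assessment is stated for these carers.
- **Carers with active issues.** For them "a 6 month assessment will be completed (to be used in main data analysis"), and a separate final assessment follows when the episode ends.
- **Carers whose caring role changes.** If the care recipient dies or moves permanently to residential care, the carer may continue "or to cease involvement with the CHWS (with re-assessment at this time point if this is acceptable to the carer").
- **Analysis.** Data analysis describes "Extracted data for the CHWS evaluation comparing baseline and 6 month assessment data".
- **Economics.** Table 1 describes a survey of "health care utilisation data including emergency department and hospital admissions over the past 6 months". The implementation outcomes section sets a 12-month horizon, split evenly before and after the first appointment. It derives QALYs from the utility change between the initial and 6-month assessments.

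**The concern.** The rule is one-sided. Carers who feel their needs are met are measured when they say so; carers still working on problems are measured at a fixed date. The protocol already recognises that an assessment timed by discharge should not replace the 6-month score, because it keeps the two apart for carers who run past 6 months. It gives early finishers no such protection.

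The trigger for early measurement is also close to something recorded at follow-up. Of the needs tool the protocol says "at the 6 months assessment it will only be used to ask carers if the initially prioritised needs have been (1) fully addressed", or partly addressed, or unchanged. So measurement time is linked to how well the carer is doing. In a one-group pre-post design no comparison arm shares the distortion and cancels it.

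Two things are at stake. The first is what the PCS and EQ-5D-5L changes mean: change to 6 months, or change to a mixture of times that depends on progress. The second is the cost comparison, because a fixed 6-month look-back from an early assessment reaches into the period before the service began.

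**Working it through.** **1. The stated cost horizon.** Count months from the first appointment. The baseline survey covers −6 to 0. A follow-up at month t with a 6-month recall covers t−6 to t. Then:

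- distinct months covered = 6 + t
- pre-service months counted twice = 6 − t
- post-service months never observed = 6 − t

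At t = 6 this gives 12 distinct months and no overlap, which reproduces the protocol's 12-month horizon.

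**2. The same survey brought forward.** Let the monthly event rate be r0 before and r1 after the first appointment, each constant (assumption). The baseline count is 6·r0. The follow-up count is (6−t)·r0 + t·r1. The measured change is t·(r1−r0) against a true change of 6·(r1−r0), so the share retained is t/6.

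| Follow-up month | Distinct months | Counted twice | Unobserved | Share of true change retained |
|---|---|---|---|---|
| 6 | 12 | 0 | 0 | 100% |
| 5 | 11 | 1 | 1 | 83% |
| 4 | 10 | 2 | 2 | 67% |
| 3 | 9 | 3 | 3 | 50% |
| 2 | 8 | 4 | 4 | 33% |

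These shares apply to brought-forward carers only. If a fraction f is brought forward, the sample retains 1 − f·(1 − t/6). The document does not give f or t. For f from 10% to 50% and t from 5 to 2 (assumed), the result runs from 1 − 0.1·(1/6) = 98% to 1 − 0.5·(4/6) = 67%.

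**3. QALYs.** Assume a utility gain of 0.05 seen at month 3, reached linearly.

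- Treated as a 6-month value: 0.05 × 0.5 / 2 = 0.0125
- Area to month 3 only: 0.05 × 0.25 / 2 = 0.0063
- Gain held from month 3 to month 6: 0.00625 + 0.05 × 0.25 = 0.0188

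The same observation gives three answers, depending on how the missing months are treated.

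**4. PCS.** If early assessments enter the comparison as 6-month values, bias = f × (score at exit − score at 6 months). Neither term is in the document.

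- Gains fade: assuming f = 0.2 to 0.4 and a loss of 0.1 to 0.3 item points, the bias is 0.2 × 0.1 = 0.02 to 0.4 × 0.3 = 0.12. The improvement cited under Sample size calculation is 0.2.
- Gains hold: the bias is 0.
- Gains keep growing: the bias is negative.

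Fluctuation alone can also produce a gain. A simulation used 200,000 carers, the cited SD of 0.57 and no true change. It assumed a within-person correlation of 0.5 or 0.7, a needs-met signal correlated 0.5 or 1.0 with the momentary PCS deviation, and checks at months 3 to 5. About 19–40% were brought forward, and the spurious gain was 0.06 to 0.25. With everyone measured at month 6 it was 0.00. This shows that the mechanism works; it does not estimate its size in this study.

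**The case against.** The strongest reply is that this is a pragmatic service evaluation, that assessing at the end of an episode is a recognisable choice, and that the number affected may be small. Handling of off-schedule assessments is often left to an analysis plan, which is not shown. Much of this stands, and it limits what can be claimed.

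- **Entry into the main analysis is inferred.** The protocol does not say how brought-forward assessments, or those taken when a carer leaves after a death or residential move, are analysed. For early finishers the inference is natural, because no other post score is planned. Leaving them out would remove carers who did well and sit badly with the stated intention-to-treat basis.
- **The trigger is not the PCS.** It is a feeling that needs are met, and Table 1 says the needs tool is not an outcome measure. A link to the PCS is plausible but not stated.
- **A reader might infer that the PCS change is biased upward by a known proportion.** The documents do not support that. Upward bias needs gains that fade or fluctuate, and the upper fade assumed above (0.3) is 1.5 times the whole cited improvement.
- **A reader might infer that the cost overlap flatters the service.** Under constant rates it pulls the change in use toward zero, so it would hide a reduction. It is clear only for emergency and hospital items; care hours are weekly averages and intervention costs are a separate item. The follow-up questionnaire wording is not shown.

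One part of the reply fails. The timing rule governs data collection, and no analysis plan can recover a 6-month score that was never collected.

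**Conclusion.** The point holds as a mismatch between the assessment rule and the quantities the protocol says it will estimate. Early finishers have no stated 6-month score, and their only post score is taken at a self-declared good point. That fits neither the baseline-versus-6-month comparison nor the 6-month utility change. It can favour the service on PCS and EQ-5D-5L if gains fade or fluctuate; size and direction are not determinable from the document.

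The recall problem is arithmetic, provided the survey keeps its fixed 6-month look-back at an early follow-up: 6−t months double-counted and 6−t missed. Retaining t/6 of the true change also assumes constant rates within each period.

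This is a cheap improvement. The documents do not show that the primary result is invalid.

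**What to change.** Collect the core outcome set (PCS, EQ-5D-5L, Family Appraisal of Caregiving Questionnaire and utilisation survey) at 6 months after the initial assessment from every consenting carer, whatever the discharge date, and use it in the main analysis. Keep any earlier discharge assessment, or re-assessment when the caring role changes, as an additional record. This mirrors what is already done for carers who continue past 6 months. Discharge decisions are unchanged.

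For early assessments already done with no 6-month contact:

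- record exact dates;
- tie utilisation recall to the first appointment, so that pre-service events are not counted again;
- compute QALYs from actual time;
- run a sensitivity analysis excluding these carers.

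The cost is one extra remote questionnaire contact, a minor ethics amendment and some non-response among discharged carers. Table 1 marks all four core instruments as remote or questionnaire-based. Recruitment ends on 31 May 2025, so a 6-month contact falls by about the end of November 2025 if the initial assessment follows promptly. That is before the stated project end in December 2025.
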